**Discussion:**

Persistent wrist arthritis continues to be a problem for patients with rheumatic joint disease leading to disability. This is the first randomized controlled trial to evaluate the effect, safety and feasibility of arthroscopic synovectomy of the wrist in these patients compared to IACSI.

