When individual arthritic joints remain refractory to drug therapy, surgical approaches may be indicated to preserve joint function, prevent further destruction of tendons and relieve pain [13, 14]. Tendon reconstruction, wrist arthroplasty or arthrodesis are only indicated for advanced stages of wrist arthritis due to their disabling consequences and high risk of complications [3, 15]. Synovectomy of the wrist aims to relieve symptoms and prevent disease progression by debulking inflamed synovial tissue. Arthroscopic synovectomy has shown clear advantages over open synovectomy as it renders minimal postoperative pain, early rehabilitation, faster recovery and less restriction of joint motion [13, 16]. Therefore, open synovectomy has largely been abandoned. A recent systematic review included six studies with a total of 153 wrists of RA patients that underwent arthroscopic synovectomy [17]. Improvements of wrist pain and functionality were observed after a mean follow-up of 4 years with only two complications. However, since RCTs were not available, findings were based on non-comparative cohort studies and the risk of bias was high. The efficacy, adverse effects and feasibility of arthroscopic synovectomy in rheumatic wrists remain to be investigated.

Poor response rates to DMARD therapy in RA and PsA patients have necessitated the identification of pathobiological biomarkers and immunological features that predict the outcome of treatment with biological (and targeted synthetic) DMARDs. Implementing these profiles for therapy may ultimately lead to personalized medicine and improved patient care [18, 19]. The synovium is the primary site of inflammation of RA; therefore, synovial biopsies are superior to blood or skin samples for these analyses [19]. Preferably, tissue from biological-naïve patients is used for this.

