## Trial design {8}

The ARCTIC trial is a non-blinded, two-arm randomized controlled trial comparing arthroscopic synovectomy to IACSI of the wrist. The patient allocation ratio is 1:1. Patients of both groups are allowed to cross over after 3 months if clinically indicated.

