### Sample size {14}

The sample size was calculated for the primary endpoint, the difference in PRWE scores at 3 months. According to one study, the median PRWE score in RA patients is 20.0 (IQR: 9.8–48.3) for the dominant hand and 22.8 (IQR 6.9–38.6) for the non-dominant hand, but means and standard deviations for RA are not known [27]. The mean PRWE score among the general population was estimated as 7.7 with a standard deviation of 15.0 [28]. The minimal clinically important difference of the PRWE is 11.0 points [29]. We hypothesize that a mean difference of at least 11.0 points on the PRWE score could be encountered between the two groups after 3 months. A simulation study using *K* = 1000 random draws per sample size from a multivariate normal distribution was performed to estimate the power for several sample sizes, where the significance of the treatment effect was estimated by a linear mixed model (likelihood ratio test). Assuming a (conservative) correlation of 0.1 between PRWE at baseline and at 3 months and a standard deviation of 15.0, it was found that at *α* = 0.05 and power of 90%, 38 patients per treatment arm would be required. To correct for the expected loss to follow-up of 5%, 40 patients in each arm will be included.

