## Statistical methods

### Statistical methods for primary and secondary outcomes {20a}

The primary analysis will be performed according to the intention-to-treat principle. A per-protocol analysis will also be conducted accounting for possible cross-over patients. A description of the planned intention-to-treat and per-protocol analyses for outcome PRWE conform to the estimands framework is provided as a supplementary file [42, 43]. Baseline patient characteristics will be analysed using simple descriptive statistics. Differences in the change in the primary outcome (PRWE at 3 months minus PRWE at baseline) between the two groups will be analysed using a linear mixed model, including the baseline measurement in the outcome vector and stratification variable disease (RA/PSA), time and treatment × time interaction as covariates. The difference in the change in PRWE score will be considered statistically significant if *p* < 0.05 (likelihood ratio test). The model will be extended by including the other time points to assess further trends in the development of PRWE scores. The secondary outcomes, EULAR response rate, DAS28 scores, EQ-5D-5L scores, range of motion (ROM), grip strength and pain (NRS) will be analysed in a similar manner. Differences between the two treatment groups in rates of complications and secondary interventions will be analysed using Pearson’s chi-square test or Fisher’s exact test. IBM SPSS (version 23.0, Chicago, IL) or similar software will be used for analysis.

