## Discussion

This study is designed to evaluate arthroscopic synovectomy for the treatment of rheumatic wrist arthritis. Wrist arthroscopy is a minimally invasive procedure often used by wrist surgeons to diagnose post-traumatic wrist pathology, repair ligament tears and resect ganglion cysts [44–46]. Earlier studies have demonstrated improvement of wrist function and pain after arthroscopic synovectomy in RA patients [17, 47]. It is suggested that arthroscopic synovectomy can be beneficial in both early- and late-stage wrist arthritis [48, 49]. There is, however, a lack of high-quality studies and this will in fact be the first comparative trial on the topic. Other therapies such as IACSI and radiosynoviorthesis have not proven ideal for the management of local arthritis due to high recurrence rates [9, 10, 50]. Results of this study could provide rheumatologists and wrist surgeons with a safe and effective alternative to treat wrist arthritis. If disease progression can be slowed down, arthroscopic synovectomy could also prevent long-term morbidity, the need for additional treatment and healthcare expenses. Additionally, this study allows for the collection of valuable synovial tissue samples, which may enable the development of prediction models for anti-rheumatic therapy response. This will be tested in a soon expected pilot study with a selected number of patients. Future research plans include a prospective cohort study to evaluate the feasibility and outcome effect of biopsy-driven prediction models.

There is little research on aetiology, presentation and treatment of PsA in comparison to RA, which is why it is included in this study. PsA predominantly presents with an asymmetric oligoarticular arthritis and features nail disease, skin lesions and axial skeleton inflammation [51, 52]. However, similar to RA, PsA is characterized by hyperproliferation of multiple joints and wrist arthritis is a common feature.

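### The complications test in {20a} cannot by itself answer the article's question about safety against IACSI; base that answer on a risk difference with a 95% interval

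*Protocol article*

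**What the plan says.** The protocol article makes safety part of the trial's purpose in three places:

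- Abstract, Discussion (the comparator named there is IACSI): "This is the first randomized controlled trial to evaluate the effect, safety and feasibility of arthroscopic synovectomy of the wrist in these patients compared to".
- Background and rationale {6a}: "The efficacy, adverse effects and feasibility of arthroscopic synovectomy in rheumatic wrists remain to be investigated".
- Main Discussion: "Results of this study could provide rheumatologists and wrist surgeons with a safe and effective alternative to treat wrist arthritis".

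Complications are listed as a secondary outcome under Outcomes {12}. Their analysis is given in one sentence of section {20a}: "Differences between the two treatment groups in rates of complications and secondary interventions will be analysed using Pearson’s chi-square test or Fisher’s exact test". That sentence gives no effect measure, interval, margin or rule for choosing between the two tests.

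Sample size {14} is derived from PRWE only: "38 patients per treatment arm would be required", and after allowance for 5% loss, "40 patients in each arm will be included". No power or precision is stated for complications.

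**The concern.** A test of difference answers whether the data show unequal rates. It can reveal a large excess of complications. A non-significant result shows only that the data are compatible with no difference, and in a small trial with few events they are also compatible with a sizeable one. The question the article raises is how large an excess of complications arthroscopy might carry, and the named method gives no figure for that.

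At this sample size a non-significant result is likely in many situations where a relevant excess exists. If the trial report then says only that complications did not differ significantly, readers may take an operation under general or regional anaesthesia to be as safe as a five-minute injection, when the data have not excluded a material difference.

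**Working it through.** **Inputs.** From the article: 38 evaluable and 40 randomized per arm, ratio 1:1 (Sample size {14}, Trial design {8}). Assumed: two-sided alpha 0.05 for the complications test, since none is stated for it, and complication rates of 1% and 10%. The article gives no expected rate for either arm and no IACSI rate at all. Its only usable figure is two complications in 153 wrists (2/153 = 1.3%, exact 95% interval 0.2% to 4.6%). That figure comes from arthroscopy cohorts with a high risk of bias, so it cannot stand in for the IACSI arm.

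**1. The plan's own figure.** With the baseline in the outcome vector, the effective SD is 15 × √(1 − 0.1²) = 14.92. Then n = 2 × [14.92 × (1.960 + 1.282) / 11]² = 38.7, or 39 per arm against 38 stated; power at 38 is 89.5%. Loss adjustment: 38 / 0.95 = 40. The stated size is reproduced to within one patient, and it depends on nothing but PRWE.

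**2. Power of the named tests.** For every pair of counts (a, b), take the product of the two binomial probabilities and sum over the pairs with p < 0.05.

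| Assumed rates | n per arm | Fisher power | Uncorrected Pearson power |
|---|---|---|---|
| 10% vs 1% | 40 | 15.0% | 44.4% |
| 10% vs 1% | 38 | 12.8% | 41.3% |
| 10% vs 5% | 40 | 4.3% | 14.6% |
| 15% vs 1% | 40 | 45.3% | 74.9% |
| 20% vs 1% | 40 | 73.6% | 90.9% |
| 25% vs 1% | 40 | 90.1% | 97.2% |

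For 10% vs 1%, Fisher misses 85% (n = 40) to 87% (n = 38) and uncorrected Pearson 56% to 59%. The expected number of events per arm is 40 × (0.10 + 0.01) / 2 = 2.2. At expected counts below 5, convention points to Fisher, but the article does not fix that rule. The usual normal-approximation formula needs about 100 per arm for 80% power at these rates.

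**3. Single results, 40 per arm.**

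- 5/40 vs 0/40: Fisher p = 2 × C(40,5) / C(80,5) = 0.055.
- 4/40 vs 1/40: Fisher p = 0.36; Newcombe 95% interval for the difference −4.5 to +20.7 percentage points.
- 1/40 vs 1/40: Fisher p = 1.00; interval −10.6 to +10.6 points.
- 0/40 in one arm: exact two-sided 95% upper limit 1 − 0.025^(1/40) = 8.8%.

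The last three results are all unremarkable by the test, yet the intervals show how much remains unexcluded.

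**The case against.** **No rule equates non-significance with safety.** A reader might infer that the article treats safety as a settled conclusion, or plans to declare it when p > 0.05. The text does not support this. Safety is something to be evaluated in the Abstract and a conditional hope in the main Discussion, and section {20a} names a test without saying how a null result will be read. This objection stands; the point is only that the test cannot supply the answer sought.

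**Reporting detail may sit elsewhere.** The full protocol and any analysis plan are not shown and may contain intervals. This stands too, so the test can be called only the one analysis the article describes. But the article does not leave the method open: it names one, and that one does not fit the question.

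**The miss rate depends on the test and on assumed rates.** It would be wrong to say that either test misses 10% vs 1% almost nine times in ten; that holds for Fisher only. It would also be wrong to treat 2/153 as the article's low rate for IACSI. That figure belongs to arthroscopy, and even its upper 95% limit of 4.6% lies below the 10% assumed here for the worse arm. The contrast is an illustration, and for very large excesses (25% vs 1%) even Fisher has about 90% power.

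**Low power for a secondary safety outcome is ordinary.** True, and no power was promised. That is a reason to estimate the difference rather than rely on a test.

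**Conclusion.** The point holds as a cheap improvement to the analysis. The method named for complications can detect a large excess of harm, but it cannot support a statement that arthroscopic synovectomy is as safe as IACSI. With 38 to 40 per arm and assumed rates of 10% and 1%, an excess of nine percentage points would go undetected in 85% to 87% of trials with Fisher and in 56% to 59% with uncorrected Pearson. The range in the table shows how this moves with the rates. The conclusion that a non-significant test is not evidence of equal safety does not depend on any one pair of rates.

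**What to change.** In section {20a}, replace the test as the basis for the safety statement:

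- Report the number and percentage of patients with at least one complication in each arm.
- Report the risk difference, arthroscopy minus IACSI, with a 95% Newcombe or exact interval. Name the interval method in advance, because method and test can disagree at borderline counts: for 5/40 vs 0/40 the Newcombe interval is +1.3 to +26.1 points although Fisher gives p = 0.055.
- Base the safety statement on that interval and its upper limit, which is the largest excess the data do not exclude.
- Add a sentence such as: *A non-significant test of complication rates will not be taken as evidence that the two treatments are equally safe.*

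The chi-square or Fisher test may stay as a check for harm. The hoped-for safe alternative in the main Discussion should be tied to the upper limit.

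The cost is a few sentences and one interval in the results table, with no new data or patients. The downside is a more modest safety statement, since even a complication-free arm of 40 leaves an upper limit of about 9% for that arm.

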### Sequence generation {16a}

Randomization will be performed using a computerized randomization procedure in Castor EDC [30]. Patients will be randomized in a 1:1 ratio using variable block sizes of two, four and eight patients, stratified for disease type (RA or PSA) to avoid imbalances between groups. The order of the block sizes is unknown to the researchers.

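### Secondary-intervention and complication rates are compared with an unstratified test although randomisation is stratified by disease; this costs power only if RA and PsA rates differ substantially (minor)

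*Protocol article*

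**What the plan says.** Under Sequence generation {16a}: "Patients will be randomized in a 1:1 ratio using variable block sizes" of two, four and eight, and the randomisation is "stratified for disease type (RA or PSA) to avoid imbalances between groups".

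Under Statistical methods for primary and secondary outcomes {20a}, the linear mixed model for PRWE has "stratification variable disease (RA/PSA), time and treatment × time interaction as covariates". EULAR response, DAS28, EQ-5D-5L, range of motion, grip strength and pain are to be handled in like fashion. For the remaining binary comparisons the same section fixes a different approach: "rates of complications and secondary interventions will be analysed using Pearson’s chi-square test or Fisher’s exact test". Disease is not mentioned there.

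The Objectives {7} list secondary drug treatment and secondary surgery among the things to be evaluated. Limitations adds that one aim is to see how far synovectomy can prevent bDMARD use.

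**The concern.** Blocking within RA and within PsA makes the two arms nearly identical in disease mix. Differences between the diseases therefore contribute almost nothing to the difference between arms. A pooled chi-square still counts that between-disease variation in its variance. If the diseases have different event rates, the variance is too large, the test rejects too rarely under the null, and power falls.

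Secondary interventions need not be rare. The Background reports reduced swelling and tenderness in 40–50% of injected joints at 3 months and relapse in up to 40% within 12 months, and cross-over is allowed after 3 months. At stake is some power on a secondary comparison in a trial of 80 patients, and consistency between the randomisation, the PRWE model and this test.

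**Working it through.** **The plan's own figure.** The article gives a sample size for PRWE only. With the stated SD of 15.0, correlation of 0.1 and difference of 11.0:

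n = 2(1.96 + 1.2816)² × 15² × (1 − 0.1²) / 11² = 21.02 × 222.75 / 121 = 38.7, so 39 per arm.

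A 20,000-draw simulation of the likelihood ratio test gives power 0.891 at 38 per arm. This agrees with the stated 38 and 90%, and 38 / 0.95 = 40. The figure reproduces, but it says nothing about the binary comparisons, for which no power is claimed.

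**Inputs for the check.**
- From the documents: two arms, "To correct for the expected loss to follow-up of 5%, 40 patients in each arm will be included"; stratification by disease; unstratified test. A two-sided 0.05 level is used.
- Assumed, because the documents do not give them: 30% PsA (28 RA and 12 PsA per arm), exact balance within disease, the control event rates below, and a common odds ratio of 0.3 for power.

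**Large-sample size.** With disease shares w and event rates p:
- within-disease variance = Σ w p(1 − p)
- pooled variance = p̄(1 − p̄), where p̄ = Σ w p
- true size of the pooled test ≈ 2Φ(−1.96 / √ratio), with ratio = within / pooled

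RA 30%, PsA 60%: p̄ = 0.7 × 0.30 + 0.3 × 0.60 = 0.39. Within = 0.7 × 0.21 + 0.3 × 0.24 = 0.219. Pooled = 0.39 × 0.61 = 0.2379. Ratio 0.921, size about 0.041.

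RA 20%, PsA 70%: p̄ = 0.35. Within = 0.7 × 0.16 + 0.3 × 0.21 = 0.175. Pooled = 0.2275. Ratio 0.769, size about 0.025.

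**Exact results.** All possible outcomes were enumerated, comparing the Pearson test with the Cochran-Mantel-Haenszel (CMH) test stratified by disease:

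| RA / PsA control rate | Gap (points) | Size, Pearson vs CMH | Power, Pearson vs CMH |
|---|---|---|---|
| 30% / 30% | 0 | 0.048 vs 0.049 | 0.554 vs 0.554 |
| 30% / 40% | 10 | 0.047 vs 0.048 | 0.582 vs 0.584 |
| 35% / 50% | 15 | 0.049 vs 0.050 | 0.634 vs 0.641 |
| 30% / 50% | 20 | 0.045 vs 0.048 | 0.595 vs 0.606 |
| 40% / 60% | 20 | 0.052 vs 0.052 | 0.667 vs 0.679 |
| 30% / 60% | 30 | 0.042 vs 0.048 | 0.588 vs 0.618 |
| 20% / 70% | 50 | 0.024 vs 0.050 | 0.434 vs 0.530 |
| 2% / 5% | 3 | 0.018 vs 0.017 | 0.020 vs 0.020 |

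**Sensitivity.** With RA:PsA per arm of 30:10 or 20:20 and an odds ratio of 4, gaps of 10 to 20 points cost 0 to 1.5 points of power. A 40-point gap (10% vs 50%) costs about 8 to 9 points (0.613 vs 0.706 and 0.671 vs 0.748), with Pearson size 0.028 to 0.030. At low rates with a 10-point gap (5%/15%, 10%/20%) Pearson size is 0.051 to 0.056, so it is not conservative there. At 5% in both diseases CMH has slightly less power than Pearson (0.444 or 0.433 against 0.458).

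Fisher's test is more conservative throughout: size 0.004 at 5%/5% and 0.028 at 20%/20%. That comes from discreteness and is present with no difference between the diseases.

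**The case against.** The strongest reply is that nothing in the article points to a large gap between RA and PsA. The response and relapse figures in the Background are pooled over injected RA and PsA joints, and the Discussion stresses similarities between the diseases as well as differences. A reader might take those figures as evidence that the strata differ. They suggest only that events could be common, and joint non-response or relapse is not itself a re-intervention rate. This objection stands: the size of the loss is unknown and could be nil.

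Second, for complications the issue is close to empty. The Background cites two complications in 153 wrists (1.3%). At such rates sparse data determine the result and stratification changes nothing useful. This also stands.

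Third, these are secondary comparisons with no stated hypothesis or power, and supportive analyses are often left to an analysis plan that is not shown. This stands in part. The article does not leave the test open, however: it names an unstratified one, in the section that adjusts the other named outcomes for disease.

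**Conclusion.** The point holds as a minor one. The planned test does not use the stratification factor, and it loses power if RA and PsA re-intervention rates differ substantially: about 0 to 1.5 percentage points for gaps of 10 to 20 points, about 3 for 30 points and about 10 for 50 points. These figures assume 40 per arm, 30% PsA, balanced strata and an odds ratio of 0.3. With equal rates or rare events there is no gain.

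Three stronger readings are not supported:
- That the p-value is invalid. The comparison between arms is unbiased, and the highest Pearson size found was 0.056.
- That the test is too conservative whenever the diseases differ. At gaps of 10 to 20 points its size was 0.043 to 0.056.
- That a key secondary outcome is compromised. The article does not rank its secondary outcomes.

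The primary PRWE conclusion is unaffected.

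**What to change.** In Statistical methods {20a}, state that secondary-intervention rates will be compared with a Cochran-Mantel-Haenszel test stratified by disease (RA/PsA), and that the exact stratified version will be used when events are sparse, as is likely for complications.

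This is one line of wording and needs no extra data or patients. With moderately frequent events and equal rates in the two diseases it costs nothing (0.554 vs 0.554). With very sparse events it can give up a point or two of power (0.458 vs 0.444 or 0.433 at 5% in both diseases), so for complications the reason to stratify is consistency with the randomisation, not efficiency.

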### Interim analyses {21b}

Since the trial compares two low-risk interventions, both of which are implemented as safe and effective approaches of standard care in the Maasstad Hospital, no interim analyses or formal stopping rules were included.

### Methods for additional analyses (e.g. subgroup analyses) {20b}

Subgroup analyses with regard to the PRWE score will be performed on type of pathology (RA or PsA), gender and age (18–65 years and > 65 years). Values of *p* < 0.05 will be considered statistically significant.

#### Cost-effectiveness analysis

Costs include direct medical costs (professional time, laboratory tests, diagnostic procedures, drug therapies, medical admissions and surgical admissions), direct non-medical costs (help at home and selfcare, help devices, transportation and home remodelling) and indirect costs (lost productivity in employed patients, lost productivity in family members caring for the patient). The direct costs of each patient will be obtained from the financial data of the Maasstad Hospital. The indirect costs of each patient will be measured on the basis of the filled-out iMTA Medical Consumption Questionnaire (iMCQ) and iMTA Productivity Cost Questionnaire (iPCQ) questionnaire. These measured costs will be valued with the friction cost method.

After all the costs and utilities are obtained, the incremental cost-effectiveness ratio (ICER) will be calculated with the following formula:$$\mathrm{ICER}=\frac{\mathrm{Cost}\;\mathrm{of}\;\mathrm{arthroscopic}\;\mathrm{synovectomy}-\mathrm{Cost}\;\mathrm{of}\;\mathrm{IACSI}}{\mathrm{Effect}\;\mathrm{of}\;\mathrm{arthroscopic}\;\mathrm{synovectomy}-\mathrm{Effect}\;\mathrm{of}\;\mathrm{IACSI}}$$

